### Data analysis

#### Diagnostic study

The final TIA diagnosis will be presented as frequencies of the composite of TIA or minor stroke versus other diagnoses. The parameters of routine clinical assessment (symptoms and signs) of the GP and the mean biomarker values will be presented for subjects with a TIA/minor stroke and subjects with other diagnoses. First, the positive and negative predictive value and sensitivity and specificity will be assessed as test characteristics of all diagnostic tests/biomarkers.

Multiple logistic regression analyses with and without biomarker test results will be performed after multiple imputation of missings, to quantify the diagnostic accuracy of the routine clinical assessment by the GP (first model) and the improvement of diagnostic accuracy by adding biomarker assessment to this clinical assessment (additional models). Overall diagnostic accuracy of the models (after adjustment for over-optimism using bootstrapping techniques) will be quantified by assessing and comparing their calibration (applying the Hosmer-Lemeshow test) and discrimination (using ROC area or C-statistics) and classification across various probability cut-offs (e.g. using the integrated discrimination index and the net reclassification improvement).

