**Methods/design:**

Study design: a cross-sectional diagnostic accuracy study with an additional six month follow-up period.

Study population: 350 patients suspected of TIA in the primary care setting.

Patients suspected of a TIA will be recruited by at least 200 general practitioners (GPs) in the catchment area of seven TIA outpatient clinics willing to participate in the study. In all patients a blood sample will be drawn as soon as possible after the patient has contacted the GP, but at least within 72 h after onset of symptoms. Participants will be referred by the GP to the regional TIA outpatient clinic for additional investigations, including brain imaging. The ‘definite’ diagnosis (reference standard) will be made by a panel consisting of three experienced neurologists who will use all available diagnostic information and the clinical information obtained during the outpatient clinic assessment, and a six month follow-up period. The diagnostic accuracy, and value in addition to signs and symptoms of candidate serum biomarkers will be assessed in terms of discrimination with C statistics, and calibration with plots.

We aim to include 350 suspected cases, with 250 patients with indeed definite TIA (or minor stroke) according to the panel.

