### Sample size calculation

Our sample size calculation is based on the primary research question to be able to answer whether any of the biomarkers has added diagnostic value beyond the clinical assessment. We applied Harrell’s rule of thumb [15] that may be used for power calculations in diagnostic and prognostic studies. This rule states that for every determinant considered for multivariate logistic regression analysis at least ten subjects are needed in the smallest category of the outcome variable.

On a TIA service the diagnosis of TIA is confirmed by the neurologist in around 70 % of patients referred by the GP [11, 16]. About 30 % of patients will be diagnosed as non-TIA (the latter being the smallest outcome category).

Following these proportions and because we evaluate up to 10 potential diagnostic determinants, 100 non-TIA patients are required. This means that we need a total of (100 x (1/0.3)=) 333 patients suspected of TIA. To be on the safe side and to allow for some ‘loss to follow-up’ and missing of essential endpoints, we aim to include 350 patients.

In case the proportion of non-TIA patients is higher than 30 %, less than 350 suspected TIA will suffice: we will stop inclusion after a total of 100 non-TIA patients have been verified by the panel and included in the study.

We realize that the power is insufficient for answering the secondary research question on prognosis based on an expected incidence of 20–30 follow-up events in six months. At the best, two or three predictors could be evaluated in multivariable regression analysis. The results on prognosis will therefore be hypothesis generating rather than hypothesis testing.

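### The Methods name only the Hosmer-Lemeshow test for assessing and comparing calibration; its p-value has no size or direction, is hard to correct for optimism, and replaces the plots named in the abstract.

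*Protocol article*

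**What the plan says.** The Diagnostic study subsection plans logistic models of the GP's clinical assessment, then further models that add biomarkers: "Multiple logistic regression analyses with and without biomarker test results will be performed after multiple imputation of missings". The sentence on performance begins "Overall diagnostic accuracy of the models (after adjustment for over-optimism using bootstrapping techniques) will be quantified". It then lists three components: calibration, discrimination (ROC area or C statistic) and classification across probability cut-offs. For calibration the only tool given is the one in "assessing and comparing their calibration (applying the Hosmer-Lemeshow test". No plot, slope or intercept appears in that section.

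The abstract describes the same analysis differently: accuracy and added value "will be assessed in terms of discrimination with C statistics, and calibration with plots".

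The Sample size calculation sets the scale: "because we evaluate up to 10 potential diagnostic determinants, 100 non-TIA patients are required", with a planned total of 350.

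**The concern.** The plan gives the calibration measure two jobs. It must be adjusted for over-optimism, and it must compare models with and without biomarkers. A Hosmer-Lemeshow p-value suits neither.

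- **Optimism.** A maximum-likelihood logistic model fits its own data with a calibration slope of exactly 1. Overfitting appears as a slope below 1 in new patients. The test on the fitted data does not see this, and its p-value, unlike a slope, has no standard bootstrap correction.
- **Comparison.** The p-value does not say whether predictions are too extreme or too moderate, or by how much. A larger p-value for one model is not evidence that it is better calibrated.

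The stake is the comparison at the heart of the primary objective. If the biomarker models carry more predictors than the clinical model, they tend to overfit more, and a check that does not register overfitting cannot show the difference. The planned reclassification measures also work on predicted probabilities, so their meaning depends on calibration.

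**Working it through.** **The plan's own figure.** Ten determinants at ten subjects each in the smaller outcome group gives 10 × 10 = 100 non-TIA patients, and 100 / 0.30 = 333.3. The stated 333 is reproduced. At 350 patients, 350 × 0.30 = 105 non-TIA are expected. This sets the scale but does not bear on calibration, for which the article gives no figure, so the check is by simulation.

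**Inputs from the article.** N = 350; 30% non-TIA; up to 10 determinants; logistic regression; bootstrap optimism adjustment.

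**Assumptions, not in the article.** True C statistic about 0.70 or 0.75; independent normal predictors, half of them noise; and, as an alternative to 10, a count of 17 predictors (the seven named biomarkers plus 10 clinical items).

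**Formulas.**
- Hosmer-Lemeshow on the fitted data, 10 groups: X² = Σ (O − E)² / [E(1 − E/n)], summed over groups of size n with observed count O and expected count E; 8 degrees of freedom.
- Calibration slope b: logit P(TIA) = a + b × LP, where LP is the model's linear predictor. In the fitted data the likelihood equations force a = 0 and b = 1.
- Bootstrap-corrected slope: refit in each bootstrap sample and take the slope of that model in the original patients. Each refitted model has slope 1 in its own sample, so optimism = 1 − mean slope, and the corrected value = 1 − (1 − mean slope) = mean slope.

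**Results, two sets of runs (A: 400 per setting; B: 600 per setting).**

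| Set | Predictors | Assumed C | Test rejects, fitted data | Slope, new patients | Bootstrap slope |
|---|---|---|---|---|---|
| A | 10 | 0.70 | 5.5% | 0.76 | 0.79 |
| B | 10 | 0.70 | 5.5% | 0.78 | 0.80 |
| B | 10 | 0.75 | 4.7% | 0.83 | 0.84 |
| A | 17 | 0.70 | 6.5% | 0.64 | 0.70 |
| B | 17 | 0.70 | 5.0% | 0.69 | 0.71 |
| A | 17 | 0.75 | 5.0% | 0.71 | 0.74 |
| B | 17 | 0.75 | 7.2% | 0.73 | 0.75 |

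A further set agreed: about 3% to 6% rejection; slopes of 0.77 to 0.83 (10 predictors) and 0.65 to 0.72 (17) in new patients; bootstrap slopes of 0.80 to 0.85 and 0.70 to 0.75.

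**Reading the table.** The rejection rate stays near 5% whether the slope in new patients is 0.83 or 0.64. In set B at C 0.70, going from 10 to 17 predictors lowers the slope from 0.78 to 0.69 while the rejection rate goes from 5.5% to 5.0%. The test does not tell the two models apart; the bootstrap slope (0.80 against 0.71) does. The miscalibration is real: on new samples of 350 in set A the same test, with 10 degrees of freedom, rejected in 33% (10 predictors, C 0.70), 57% (17, C 0.70) and 48% (17, C 0.75) of runs. The article describes no such independent sample.

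**The case against.** **The plan already adjusts for over-optimism.** A reader might infer that the test will be run on unadjusted development data and that overfitting is ignored. The text does not say so. The clause on bootstrap adjustment governs the whole sentence and, as worded, covers calibration. That stands. What remains is that a p-value has no standard correction of this kind. If the clause means testing a bootstrap-shrunken model in the same patients, the test still serves poorly. In set B it then rejected in 6.7% and 5.0% of runs with 10 predictors (C 0.70 and 0.75), and in 12.8% and 10.7% with 17. With 17 predictors it therefore flagged the corrected model more often than the overfitted one (5.0% and 7.2%).

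**Abstract and Methods do not contradict each other.** A plot and a test are compatible and often reported together. This stands: it is an inconsistency to align, not a contradiction.

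**The larger effect needs 17 predictors.** The article plans up to 10, speaks of several additional models, and says the marker selection is not final. Entering seven markers on top of 10 clinical items is only one possible reading. The 10-predictor rows are therefore the ones to rely on, and the point holds there too.

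**Detail belongs in the full protocol.** How the correction is carried out may indeed be set out in a document not shown, and its absence is not the criticism. The article does, however, name a specific method, and that choice can be judged.

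**Calibration is one of three components.** The C statistic, integrated discrimination index and net reclassification improvement are also planned, and no prediction rule for practice is announced. This limits the severity.

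**Conclusion.** The point holds in a limited form. The Methods fix one calibration measure, and it is poorly suited to the two tasks the same sentence sets it. On the fitted models in the only patients described, it stays near 5% rejection. Meanwhile the slope in new patients is about 0.76 to 0.83 with 10 predictors and about 0.64 to 0.73 with an assumed 17. These slopes rest on the assumed C statistic of 0.70 to 0.75 and on independent predictors, half of them noise; a different predictor count or signal would change their size. The test's insensitivity appeared in every setting tried.

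The documents do not support saying that overfitting is ignored, that the plan is bound to report good calibration, or that abstract and Methods contradict each other. The test would usually fail to detect miscalibration of this size, and the two passages need aligning. Severity is minor to moderate.

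**What to change.** In the Diagnostic study subsection, replace the Hosmer-Lemeshow test as the calibration measure. For each model, with and without biomarkers, report the bootstrap optimism-corrected calibration slope and intercept, together with the calibration plot the abstract already promises. Compare models on these estimates, not on p-values. Shrinking the final coefficients by the corrected slope is an optional addition.

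The cost is a change of wording and a little programming. The planned bootstrap samples supply the slope and intercept, and nothing changes in recruitment, data collection or sample size.

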#### Prognostic study

The nowadays advocated prognostic ABCD2-score (Age ≥ 60, Blood pressure ≥140/90 mmHg, Clinical features, Duration of symptoms, Diabetes) will be assessed in each subject. Because we expect a low number of short-term events, we will only explore the predictive ability of the ABCD2-score, the biomarkers, and ABCD2 plus biomarkers(s).

### Regulation statement

This study is conducted according to the principles of the current version of the declaration of Helsinki and in accordance with the Dutch law on Medical Research Involving Human Subjects Act (WMO).

### Ethics committee approval

Ethical approval was given by the Medical Research Ethics Committee of the University Medical Center of Utrecht, the Netherlands, on September 5^th^ 2013.

## Discussion

In the MIND-TIA study we hope to find novel biomarkers that improve the accuracy of the GP’s diagnosis in patients suspected of TIA. This would result in a more appropriate assessment of patients suspected of TIA and timely treatment, and thus improved prognosis of TIA patients.

The study will follow clinical practice. This will help future implementation of the results in daily practice. Early blood sampling is necessary because some (potential) markers of brain ischaemia can no longer be detected 72 h after the onset of symptoms and because early treatment of TIA is essential to optimize prognosis. Diagnostic research should involve patients *suspected* of a certain disease, and results of tests should be considered *in addition* to already available test results from the clinical assessment, thus following the natural diagnostic hierarchy. In our study we thus aim to evaluate the *added* value of biomarkers beyond the clinical assessment of the GP.

The success of our study depends on the shared effort of a large number of GPs. To improve participation, we facilitate the inclusion process by involving trained research nurses who do the home visits including the informed consent procedure.

In diagnostic accuracy studies creating a valid reference standard is of a major concern. Specifically in the case of TIA, an acceptable reference standard diagnosis is challenging. In lack of a single reference test or the possibility of a composite reference standard, panel diagnosis is the only acceptable method for obtaining a final TIA diagnosis [17, 18]. Our panel will evaluate diagnostic information collected through various sources (GP, research nurse and neurologist), including a clinical follow-up period of six months [19]. We aim for transparent reporting of the decision making process of the panel, including assessing its reproducibility.
